## Abstract

**Background:**

The macronutrient composition of daily meals plays a crucial role in influencing the body's metabolic responses during the postprandial phase. However, existing research on the effects of macronutrients, particularly fats and carbohydrates, has produced inconsistent findings.

**Objectives:**

This study aims to evaluate the postprandial effects of two high-protein meals—one low in fat and high in carbohydrates (HP-LF-HC) and the other high in fat and low in carbohydrates (HP-HF-LC)—on energy metabolism, appetite response, and blood markers in overweight and obese men and women without underlying health conditions.

**Methods:**

This study was conducted as an acute randomized crossover clinical trial at the Health Monitoring Center of Mashhad University of Medical Sciences (MUMS) within Imam Reza Hospital, Mashhad, Iran. A total of 30 overweight and obese men and women, meeting the eligibility criteria and free of underlying diseases, were recruited through a public call. Participants were randomly assigned to receive both intervention meals, with a washout period of at least one week between each trial.

**Results:**

The primary outcomes focused on the acute effects of the two dietary interventions on energy metabolism, particularly resting metabolic rate (RMR), and appetite response. Secondary outcomes included changes in lipid profiles, insulin, blood glucose levels, thyroid hormones, and epinephrine.

**Conclusions:**

This study aims to identify which macronutrient composition most effectively enhances resting energy expenditure. The findings could provide valuable insights for dietitians in developing more efficient dietary plans, helping overweight and obese individuals maintain an ideal weight or achieve weight loss by modifying food composition without altering meal volume.

## 1. Background

Historically, obesity and overweight were believed to primarily affect specific demographic groups. However, it is now evident that weight-related issues are widespread (1). By 2025, approximately 167 million individuals are projected to suffer from diseases related to obesity and overweight, as indicated by non-communicable diseases (NCDs) (2). The economic impact of obesity and overweight on gross domestic product (GDP) is escalating, with projections indicating it could reach 3.29% by 2060, particularly in low- and middle-income countries (3).

Recent research suggests that the causes of obesity and overweight extend beyond the simple consumption of excess calories. Factors such as food sources, preparation methods, consumption patterns, and food quality play critical roles in the physiological mechanisms influencing obesity. These factors impact metabolism and weight changes by affecting hormones, altering gut microbiota, and influencing appetite and satiety control centers (4, 5). A common approach to weight control involves consuming low-calorie diets with varying macronutrient compositions (6). While reducing energy intake can lead to weight loss, the body's adaptive mechanisms—such as reduced energy expenditure and preservation of vital energy reserves—can eventually slow or reverse this weight loss. This phenomenon is attributed to a decrease in metabolism and resting metabolic rate (RMR) over time (6, 7).

Most studies report that high-protein meals enhance thermogenesis during the acute phase following meal intake. The energy required for metabolizing protein is approximately four times greater than that for carbohydrates and 7.5 times greater than that for fat (8). However, when examining the effects of fat and carbohydrates, studies yield varying results. Some researchers assert that there is no significant difference between proteins and carbohydrates in diet-induced thermogenesis and thermogenic effects. They suggest that the consumption of high-fat diets may be associated with increased metabolism in obese subjects (9). Conversely, other studies indicate that high-carbohydrate meals exhibit a more pronounced thermogenic effect compared to high-fat meals, with no significant difference observed between normal-weight and obese individuals (10).

In a study conducted by Blundell et al., subjects who typically consumed a high-fat diet exhibited lower energy expenditure compared to those on a low-fat diet. Furthermore, the consumption of a high-fat meal was shown to increase fat oxidation and, consequently, metabolism, while carbohydrate oxidation remained similar in both groups following a high-carbohydrate meal (11).

The existing literature presents conflicting results regarding the impact of macronutrient composition on metabolic adaptation. Therefore, this study aims to evaluate the most effective macronutrient composition for promoting metabolic adaptation and facilitating weight loss.

To ensure homogeneity within our study population, we will include only overweight and obese men and women. Measurements will not be conducted during menstruation. If a female subject is menstruating at a scheduled appointment, the measurements will be postponed to a later, more appropriate time.

## 2. Objectives

The primary objective of this study is to evaluate the effects of two distinct meal compositions—high-protein, high-fat, low-carbohydrate (HP-HF-LC) and high-protein, low-fat, high-carbohydrate (HP-LF-HC) meals—on appetite response (AR), RMR, diet-induced thermogenesis (DIT), and respiratory quotient (RQ) in adults aged 18 to 65.

The secondary objective is to assess the postprandial effects of HP-HF and HP-LF meals on blood glucose, low-density lipoprotein cholesterol (LDL-C), high-density lipoprotein cholesterol (HDL-C), triglycerides (TG), serum insulin, thyroid-stimulating hormone (TSH), thyroxine (T4), and epinephrine.

## 3. Methods

### 3.1. Trial Design

This study was structured as an acute, randomized crossover clinical trial to evaluate two meals with identical protein content but differing in fat and carbohydrate proportions (HP-HF-LC and HP-LF-HC). Each participant consumed both meals on separate days, with a minimum one-week washout period between sessions to eliminate carryover effects. The stages of intervention and evaluation were outlined in Figure 1. 

**Figure 1. A157244FIG1:**
[figure not shown]
Stages of intervention and evaluation

Two days prior to the intervention, participants were contacted and instructed to abstain from alcohol consumption, strenuous physical activity, and any dietary changes until their scheduled visit. On the day of the intervention, participants were required to arrive at the Imam Reza Hospital Research Center at 7:00 a.m., using personal vehicles or public transportation while minimizing physical exertion. Participants observed a 12-hour fasting period prior to their arrival, during which they could consume only water and had to refrain from smoking. 

Upon arrival, eligibility for participation was reconfirmed, followed by the measurement of anthropometric parameters. Participants completed an appetite questionnaire and underwent an indirect calorimetry (IC) assessment in a fasting state. Immediately after the IC assessment, a venous blood sample was collected. Participants then consumed the assigned intervention meal within 10 minutes under researcher supervision. 

During the postprandial phase, IC and appetite response assessments were conducted four times at one-hour intervals. Blood samples were collected twice: One hour after the meal and again during the final hour of the assessment. All tests were performed under standardized conditions and administered by the same personnel to ensure consistency. Figure 2 provided a schedule of the intervention and assessments, with time intervals selected based on prior studies. 

**Figure 2. A157244FIG2:**
[figure not shown]
Schedule of the intervention and assessments

### 3.2. Participants, Interventions and Outcomes

#### 3.2.1. Study Setting

This randomized crossover study was conducted at the Persian Study Research Center, located at Imam Reza Hospital, affiliated with Mashhad University of Medical Sciences (Mashhad, Iran). Participants were recruited through advertisements disseminated via posters placed in healthcare centers across the city and email outreach at Mashhad University of Medical Sciences. The study was retrospectively registered with the Iranian Registry of Clinical Trials (IRCT) under registry number IRCT20240106060633N1.

#### 3.2.2. Eligibility Criteria

##### 3.2.2.1. Inclusion Criteria

The study enrolled 30 adult participants aged 18 - 65 years diagnosed with overweight or obesity, defined by a BMI range of 25 - 40. Eligible participants had not experienced weight changes exceeding 5% in the past three months. Additionally, they had not taken any medications or followed dietary interventions aimed at weight loss within the last 3 - 6 months. Participants were required to refrain from engaging in intense physical activity and were not professional athletes (MET-min < 600 min/week).

##### 3.2.2.2. Exclusion Criteria

Exclusion criteria included: (1) Meal intolerance, (2) the occurrence of adverse health events during the study, (3) engaging in heavy physical activity during the study, (4) tobacco use during the study, (5) unwillingness to continue participation. 

Patient information was recorded, and eligible participants were contacted to receive a detailed explanation of the study plan. On the day of the visit, participants signed a standard written consent form. Those who declined to provide informed consent for any reason were not included in the study. 

#### 3.2.3. Additional Consent Provisions for Data and Specimen Use

Additional consent was obtained for the collection and utilization of data and biological specimens.

### 3.3. Sample Size

Due to the novelty of our study and the absence of prior similar research, the sample size was determined based on the study by Soares et al. (12). The respiratory exchange ratio was selected as the main variable, with the alpha error set at 0.05 and the beta error at 0.2. The sample size was calculated using the two-mean test formula for a quantitative trait in two independent groups. To account for potential attrition, the final sample size was determined to be 30 participants.

$$n=\frac{{\left(Z_{1-\frac{\alpha }{2}}+Z_{1-\beta }\right)}^{2}\left(\sigma_{1}^{2}+\sigma_{2}^{2}\right)}{{\left(\mu_{1}-\mu_{2}\right)}^{2}}$$

### 3.4. Study Protocol and Ethical Approval

The study protocol was approved by the local Institutional Review Board (IRB). Informed consent was obtained from all participants or their legal guardians prior to randomization. The consent form included details about the study, outlined the use of data in the event of participant withdrawal, and granted permission for sharing relevant data with academic experts or regulatory authorities (ethics code: IR.MUMS.MEDICAL.REC.1402.411).

### 3.5. Data Collection at Baseline

At baseline, the demographic and clinical data of the participants were collected.

### 3.6. Interventions

#### 3.6.1. Intervention A

In this intervention, participants received a meal providing 25% of their daily energy requirement. The macronutrient composition of this meal included 25% protein, 45% fat, and 30% carbohydrates.

#### 3.6.2. Intervention B

In this intervention, participants also received a meal providing 25% of their daily energy requirement. However, the macronutrient composition differed, consisting of 25% protein, 15% fat, and 60% carbohydrates. 

To determine daily energy requirements, each participant's RMR was measured using an indirect calorimetry device. Total energy expenditure (TEE) was then estimated by multiplying the RMR by the thermic effect of food and a physical activity coefficient. The meals, prepared in the nutrition department's kitchen, were based on each participant's TEE and composed of ingredients supplied by a contractor. The specific composition of the meals is provided in Table 1.

**Table 1. A157244TBL1:** Macronutrient and Fiber Composition of Experimental Meals ^a^

Variables	HP-HF-LC Meal 100 (g) ^b^	HP-LF-HC Meal 100 (g) ^b^
**Moisture (%)**	68.88	70.27
**Dry matter (g)**	31.12	29.73
**Protein ** ^ ** c ** ^	10.29 (24.97)	8.26 (25.57)
**Carbohydrate ** ^ ** c ** ^	12.78 (31.01)	19.42 (60.12)
**Fat ** ^ ** c ** ^	8.05 (43.96)	2.05 (14.28)
**Energy (kcal)**	164.8	129.2
**Fiber (g)**	1.64	2.58

Abbreviations: HP-HF-LC, high-protein, high-fat, low-carbohydrate; HP-LF-HC, high-protein, low-fat, high-carbohydrate.

^a^ Values are expressed as gram (percentage of energy).

^b^ The macronutrient and fiber composition in 100 grams of the sample meals has been measured.

^c^ The amounts of macronutrients and fiber are reported in grams on a dry matter basis.

Both meals were identical in terms of ingredients. Participant feedback on the palatability and suitability of the meals was collected using a questionnaire. The quantitative specifications and micronutrient content were pre-determined by the food product manufacturer.

#### 3.6.3. Discontinuing or Modification of Interventions

Given the participants' initial dietary history and routine food intake, no complications were anticipated from the interventions. However, if any complications arose at any stage of the study, the study was promptly halted.

#### 3.6.4. Strategies to Improve Adherence to Interventions

During the registration process, participants were asked about their food preferences, interests, and allergies. The meals provided, which included toast and dairy products, were designed to align with the typical taste preferences of the target population. Individual instructions on meal consumption were given to each participant, and a designated team member was responsible for monitoring proper meal intake.

#### 3.6.5. Interventional Care

While this study was expected to involve minimal complications, participants were restricted from consuming any food or drink other than water during the study and after meal consumption. Potential complications, such as hypoglycemia or issues related to blood sampling, were anticipated, and a physician was present on-site throughout both the interventional and observational stages.

## 4. Results

The CONSORT diagram was presented in Figure 3. As this article was a protocol study, it was anticipated that the diagram would be completed upon the study's conclusion. The primary outcome of this crossover trial was to investigate and compare the postprandial acute effects of two different meals on basal metabolic rate and satiety in overweight and obese men and women. The secondary outcome evaluated the impact of these meals on various blood markers, including blood glucose, LDL, HDL, total cholesterol (TC), TG, serum insulin, TSH, T4, and epinephrine.

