### 4.5. Assessment and Outcomes

#### 4.5.1. Indirect Calorimetry Procedure

Participants began by resting in a supine position for 15 minutes to allow their heart rate to stabilize. After this period, a calorimetry mask was placed on their faces, and they breathed normally for 20 minutes. During this time, the indirect calorimetry device measured oxygen consumption and carbon dioxide production, enabling the calculation of resting energy expenditure, food oxidation rates, and respiratory rate. It was essential that participants remained awake, alert, and still throughout the calorimetry period. 

The indirect calorimetry measurements were conducted in five stages: Once before the intervention in a fasting state, and then at 1-, 2-, 3-, and 4-hours post-intervention. Due to the high sensitivity of indirect calorimetry, strict conditions were maintained to ensure maximum measurement accuracy. 

Calorimetry was performed in a separate, quiet room, isolated from other participants and distinct from the sampling area. Movements within the room were minimized, and the temperature was controlled between 22 and 24 degrees Celsius. Participants were required to fast for 10 - 12 hours before the start of the calorimetry measurement, with their evening meal being consistent with their usual diet. They were also advised to avoid strenuous physical activity on the day of the visit, arrive at the study center by vehicle, and refrain from smoking. 

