### 4.11. Expected Outcomes

#### 4.11.1. Primary Outcomes

The primary expected outcomes included the results of five indirect calorimetry measurements for each participant at each stage, as well as assessments of satiety conducted before the intervention, one hour after, and four hours after the intervention.

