## 5. Discussion

Previous attempts to combat obesity have not yielded the expected results, contributing to the current epidemic, which has emerged as a global concern. The challenges associated with obesity are complex, extending beyond immediate health issues to impose a substantial burden on society and future generations (13). Generally, obesity and overweight conditions result from an imbalance between energy intake and expenditure. A common challenge in weight loss efforts is metabolic adaptation, a process in which the body’s basal metabolic rate decreases in response to reduced food intake and caloric consumption. Exploring strategies that reduce energy intake while preserving or enhancing energy expenditure may be critical for achieving effective weight reduction and ensuring long-term maintenance (6, 14). 

Research highlights the significant role of proteins in increasing energy expenditure and promoting satiety compared to carbohydrates and fats. It suggests that increasing the proportion of protein within total caloric intake can enhance feelings of fullness, even when meal sizes are reduced (15-17). However, there is ongoing debate about whether carbohydrates or fats have a greater effect on increasing metabolic rate, particularly RMR. 

The goal of this study is to identify a protein-rich dietary composition with varying fat and carbohydrate content that optimizes RMR while minimizing any negative impacts on basal metabolism. This approach could provide an effective strategy for managing overweight and obesity without adverse side effects.

Since this is a protocol study, the actual limitations will become more evident during the implementation phase. Nonetheless, some anticipated limitations include selection bias, as individuals volunteering for this study may differ in motivation or adherence compared to the general population. Reporting bias is another potential issue, as participants self-report their food intake, which may result in less accurate data. Additionally, generalization is limited to overweight and obese populations, as the study is specifically designed to address metabolic responses within these groups. Further studies will be needed to determine whether the outcomes are consistent in other populations. These challenges will be addressed following the study to ensure the results are presented with a robust perspective.

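### The primary energy outcome is called resting or basal metabolic rate and is defined four ways, but the post-meal readings measure 4-hour postprandial expenditure, so the design cannot show that a meal raises RMR

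*Protocol article*

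**What the plan says.** The protocol article describes the primary energy outcome in four ways:

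- Abstract, Results: "energy metabolism, particularly resting metabolic rate (RMR), and appetite response".
- Section 2 (Objectives): the effect of the meals "on appetite response (AR), RMR, diet-induced thermogenesis (DIT), and respiratory quotient (RQ) in adults aged 18 to 65". RMR and DIT are separate items.
- Section 4 (Results): to "compare the postprandial acute effects of two different meals on basal metabolic rate and satiety in overweight and obese men and women".
- Section 4.11.1 (Primary Outcomes): "the results of five indirect calorimetry measurements for each participant at each stage".

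Section 4.5.1 sets the calorimetry schedule: "Once before the intervention in a fasting state, and then at 1-, 2-, 3-, and 4-hours post-intervention". It labels the derived quantity resting energy expenditure and does not separate fasting from post-meal readings.

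The aims and conclusions use the same vocabulary. The Abstract's Conclusions say: "This study aims to identify which macronutrient composition most effectively enhances resting energy expenditure". The Discussion (Section 5) seeks a composition that "optimizes RMR while minimizing any negative impacts on basal metabolism". The Background (Section 1) says the study aims to "evaluate the most effective macronutrient composition for promoting metabolic adaptation and facilitating weight loss".

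**The concern.** RMR and basal metabolic rate normally exclude the response to a meal, and this protocol uses RMR in that sense when it sizes the meals. A reading taken one to four hours after eating contains that response. If the outcome is named RMR or basal metabolic rate, a short-lived difference in the thermic effect of two meals can be read as one composition raising resting metabolism. From there it is a short step to weight maintenance or loss, which the Abstract's Conclusions raise as a practical use. At stake are the meaning of a primary outcome and of the headline conclusion.

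**Working it through.** **1. How the protocol uses RMR.** Section 3.6.2 builds total energy expenditure (TEE) by applying a thermic-effect factor and an activity factor to RMR, so RMR there excludes the thermic effect. Section 2 lists DIT beside RMR, which would be redundant if RMR included it. Section 4.5.1 requires a fast of 10–12 hours before calorimetry starts.

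**2. Count of readings (Sections 4.5.1 and 3.1).**

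| | Per visit | Per participant (2 visits) | 30 completers |
|---|---|---|---|
| Fasting, before that day's meal | 1 | 2 | 60 |
| Post-meal (1, 2, 3, 4 h) | 4 | 8 | 240 |
| Total | 5 | 10 | 300 |

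Fasting readings taken after a meal on the same day: 0. The second fasting reading follows a washout of at least one week, which Section 3.1 includes to remove any effect of the first meal. It therefore serves as a fresh baseline and not as a follow-up measurement of the first meal.

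**3. What the post-meal readings contain.** Write E0 for the fasting reading and Et for the reading at hour t. In the protocol's own terms, Et = resting expenditure + thermic effect at hour t. The meal contrast therefore bears on Et, or on Et − E0, and not on E0.

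**4. What the schedule can deliver.** With hourly readings in kcal/h and the trapezoidal rule, the increment over 0–4 h is

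DIT = (E1 − E0) + (E2 − E0) + (E3 − E0) + ½(E4 − E0) = E1 + E2 + E3 + ½E4 − 3.5·E0.

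Every term is already scheduled at both visits.

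**5. Why the label matters.** Section 1 puts the metabolic cost of protein at about 4 times that of carbohydrate and 7.5 times that of fat. Let p be the cost of protein as a fraction of its energy, and use the target compositions in Sections 3.6.1 and 3.6.2:

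- Meal A (25% protein, 30% carbohydrate, 45% fat): p × (0.25 + 0.30/4 + 0.45/7.5) = 0.385p of meal energy.
- Meal B (25% protein, 60% carbohydrate, 15% fat): p × (0.25 + 0.60/4 + 0.15/7.5) = 0.420p.
- Ratio B/A = 0.420/0.385 = 1.09, whatever p is.

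The documents' own figures thus imply a difference between meals in thermic effect with RMR unchanged.

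The absolute size needs assumptions that the documents do not give. Take p = 20–30% and TEE = 1800–3000 kcal, with the meal at 25% of TEE. The thermic effect per meal then runs from 0.25 × 1800 × 0.20 × 0.385 = 34.7 kcal to 0.25 × 3000 × 0.30 × 0.420 = 94.5 kcal. The difference between meals runs from 0.25 × 1800 × 0.20 × 0.035 = 3.2 kcal to 0.25 × 3000 × 0.30 × 0.035 = 7.9 kcal.

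**6. Metabolic adaptation and weight loss.** Sections 1 and 5 describe adaptation as a fall in metabolic rate over time or in response to reduced intake. Two single meals, each observed for four hours, do not measure it, and weight change is not listed as an outcome in Section 4.11.

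**7. Sample size.** Section 3.3 sizes the trial (30 participants) on the respiratory exchange ratio. No SD or effect for energy expenditure is given, so no sample size follows from redefining this outcome.

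**The case against.** The strongest reply is that this is a matter of naming and that the data are sound. Section 4.5.1 derives resting energy expenditure at all five stages, with participants supine, awake and still. RMR could thus be read loosely as expenditure at rest, fed or fasted. Section 4.11.1 makes all five readings primary, Section 2 already names DIT, and the analysis section (4.7) models time and type of meal. The passage on TEE in Section 3.6.2 concerns meal size and does not define an endpoint. Adaptation and weight loss appear in the Background and Discussion, not among the formal outcomes.

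Much of this stands. A reader might infer that RMR is measured only before each meal and that no scheduled reading can show a meal effect. The documents do not support that: calorimetry runs to four hours, and a meal effect on energy expenditure is obtainable. A reader might also infer that the trial is bound to report a postprandial rise as a change in RMR. No section fixes such a reporting rule, so this is a risk created by the wording. Nor does any section set a per-day unit, so an inflated 24-hour figure cannot be charged to the plan.

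The reply does not rescue the outcome definition. The loose reading conflicts with Section 2, where RMR and DIT are distinct. It cannot accommodate the word basal in Section 4. Section 4.11.1 names a set of readings that mixes fasted and fed states and does not say which contrast is the outcome.

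**Conclusion.** The point holds as a fault in the definition and labelling of a primary outcome. Four sections describe the energy outcome in four ways, and two of them name a quantity that the post-meal readings do not isolate. The design supports a comparison of 4-hour postprandial energy expenditure, or DIT, between meals. It does not support a statement that either meal raises fasting resting or basal metabolic rate, because both fasting readings precede that day's meal and the second follows the washout.

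This rests on the protocol's own separation of RMR from DIT and the thermic effect, plus the count of 2 fasting and 8 post-meal readings per participant. The 9% relative difference in thermic effect follows from the protocol's cost ratios and target compositions. The range of about 3 to 8 kcal per meal rests on assumed protein cost and TEE and is only an illustration. No data are missing and no statistical bias has been shown. The correction is still more than clerical, because it changes what the trial may conclude.

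**What to change.** - **Outcome.** In the Abstract (Results), Section 2, Section 4 and Section 4.11.1, define the primary energy outcome in the same words: postprandial energy expenditure over 0–4 h above the same-visit fasting value (DIT), in kcal per 4 h or as a percentage of meal energy. State that fasting RMR is the baseline only, and do not use basal for any fed reading.
- **Aim and conclusion.** In the Abstract (Conclusions), the closing aim of Section 1 and Section 5, limit the claim to acute 4-hour postprandial energy expenditure. Remove RMR or basal metabolism, metabolic adaptation and weight loss as things the trial can establish.
- **Cost.** Wording only. All readings are already scheduled. The downside is a narrower claim. The change should be made before results are reported.
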